### Statistics

#### Calculation of the sample size

It is planned to include a total of *N* = 50 triplets (total sample approximately 150 persons) with 50 children and adolescents (*n* = 25 per group), one attachment figure (parent or caregiver) each and, if possible, at least one associated teacher each. Estimation of sample size is based on recently published randomized controlled trials, in which the efficacy of digital treatment for children and adolescents with mental disorders is compared with control conditions [75–77] and on the anticipated number of discharges of the department during the course of the study (average treatment duration of 3 months with approximately 10 children per ward).

#### Statistical analyses

All analyses are conducted using R software [48]. All outcome variables measured pre-post-follow-up will be analyzed with separate mixed ANOVAs. Preprocessing of the data and calculation of individual values will be done according to the respective manual. Predictors will be group (intervention vs. control) and time point, as well as their interaction. Treatment success would be demonstrated by a significant interaction effect of group and time point, being shown, through adequate post hoc test, to be due to different time-effects in the two groups. We do not necessarily expect the intervention group to improve in absolute values over time, as measures can decline after discharge. Rather, we expect the intervention group to develop better over time than the control group, meaning that even a stabilization of values might be considered a success. This better development in the intervention group than in the control group should be evident in the information provided by patients themselves, as well as by parents and teachers.

The successful reintegration into daily (school) life is conceptualized besides the pre-post-follow-up assessment by the data collected in the ambulatory assessment. All ambulatory assessment data will be analyzed with multi-level models [78]. We expect the reports from patients, parents, and teachers in the intervention group to show a significantly more positive trend over time in terms of their general well-being, affect, sleep quality, school absenteeism, situation in class, and the relationship with parents, peers, and teachers, than those in the control group. Statistically, these effects are shown by a significant interaction of the within-person time trends of these reports with group membership, being due to participants in the intervention group developing better (or less bad) than participants in the control group. Variables will be adequately centered, and appropriate fixed and random effects will be included in the models.

Few missing data are expected due to ongoing monitoring. Missing data from single items of the standardized questionnaires will be handled appropriately according to the instructions in the manual. In case of complete questionnaires missing for a participant, this participant will be excluded from all ANOVAs containing this questionnaire. As multi-level models can handle missing data quite well, if they are at least missing at random, no data will be excluded from those analyses. However, appropriate variables (e.g., age, symptom severity) will be used to investigate if the missingness structure can be explained by them, rendering it to be not at random. In that case, those variables will be included in the according models to account for this non-randomness.

Due to the confidentiality of patient health data, data sets cannot be made publicly available. Access is only granted to study management who supervise data management and have a duty of confidentiality.

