
### Hypotheses

DigiPuR examines whether the reintegration of children and adolescents after their stay in a psychiatric hospital can be facilitated by digitally supported, cross-contextual aftercare. Four hypotheses emerge for the primary outcomes. First, we hypothesize readmission rates to be lower at the post- and follow-up time points in the intervention group than in the control group (treatment-as-usual; TAU). Second, we hypothesize satisfaction with treatment to be higher at the post-time point in the intervention group than in the control group. Third, we hypothesize health-related quality of life to develop better over time (pre-post follow-up) in the intervention group than in the control group. We do not necessarily expect the intervention group to improve in absolute values over time, as measures can decline after discharge, indicated by high rates of readmissions [8, 10]. Rather, we expect the intervention group to develop better over time than the control group, meaning that even a stabilization of values might be considered a success. Fourth, we hypothesize symptom severity to develop better over time (pre-post follow-up) in the intervention group than in the control group. In line with the last two hypotheses, a better development in the intervention group than in the control group is also expected for the secondary outcomes on stress, self-efficacy, and perceived competence, including ambulatory assessment on well-being, affect, sleep quality, school situation, and social relationships.

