#### Instruments

The instruments used in DigiPuR (see Table 1) are chosen to cover the five domains (symptoms, functioning, consumer perspectives, environments, systems) of the comprehensive conceptual model of outcomes of mental health care for children and adolescents [46]. The instruments and scales used in the pre-post-follow-up assessment and the ambulatory assessment are briefly described in the following, sorted according to the five domains. Item formulations were adapted where necessary so that they are understandable and suitable for both children and adolescents. Items are only presented if their content is relevant to the respective group (e.g. items on satisfaction with the program for video calls only when it was used). Primary outcomes are number of readmissions, satisfaction with treatment, health-related quality of life, and symptom severity; all others are secondary outcomes (see Table 1). As there is a great heterogeneity of diagnoses in the patient sample, the evaluation aims to assess the reintegration phase and the well-being of patients globally and across disorders. General constructs relevant to different disorders were selected and instruments were used for comparability across the age range.

**Table 1 Tab1:** Overview of assessed outcomes, assigned domains, instruments, and raters at the different study time points

Outcome	Domain [46]	Instrument or scale	Rater	Study period				
				Enrollment	Allocation	Post-allocation		
				Admission	Ambulatory assessment (2 weeks before discharge until 8 weeks after)	Pre (discharge)	Post (8 weeks after discharge)	Follow-up (24 and 36 weeks after discharge)
Symptom severity	Symptoms	DISYPS-III SCREEN [52]	CA, P*, T*	x		x	x	x
Stress vulnerability and coping strategies	Symptoms (part 1), functioning (part 2)	Adapted from SSKJ-3-8R (parts 1 and 2) [53]	CA	x		x	x	x
Self-efficacy	Functioning	WIRKSCHUL [54], WIRKSOZ [54], WIRKLEHR [54], WIRKELTERN (self-development)	CA, P, T	x		x	x	x
Health-related quality of life	Consumer perspectives, environment	KIDSCREEN-27 [55]	CA, P*	x		x	x	x
Occupational well-being	Environment	Emotional exhaustion [56], enthusiasm for teaching [56]	T			x	x	x
Satisfaction with treatment	Consumer perspectives	Adapted from FBB [57]	CA, P, T, TH				x	
Satisfaction with technical components	Consumer perspectives	SUS [58], self-development	CA, P, T, TH				x	
Expectation of change	Consumer perspectives	Adapted from patient’s expectation of change [59]	CA, P			x		

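### The group-by-time interaction that defines success does not match hypothesis 1: for readmissions its result depends on a coding the protocol does not state

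*Protocol article*

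**What the plan says.** The Protocol article names four primary outcomes (Instruments): "Primary outcomes are number of readmissions, satisfaction with treatment, health-related quality of life, and symptom severity".

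The Hypotheses section frames them in two ways:

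- **Levels.** Hypothesis 1: "we hypothesize readmission rates to be lower at the post- and follow-up time points in the intervention group than in the control group". Hypothesis 2: "we hypothesize satisfaction with treatment to be higher at the post-time point in the intervention group than in the control group".
- **Development over time.** Hypothesis 3: "we hypothesize health-related quality of life to develop better over time (pre-post follow-up) in the intervention group than in the control group". Hypothesis 4 has the same form for symptom severity.

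Statistical analyses then gives one method for the repeated assessments, "All outcome variables measured pre-post-follow-up will be analyzed with separate mixed ANOVAs", and one success rule: "Treatment success would be demonstrated by a significant interaction effect of group and time point". The rule is not restricted to particular outcomes or hypotheses. The only other method named, multi-level modelling, is for the ambulatory data, none of which is primary.

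Table 1 marks number of readmissions at admission, discharge, post and follow-up, in a row shared with general information. Satisfaction has a single mark, which agrees with the post time point in hypothesis 2. The readmission outcome is called a number (Instruments, Table 1), a rate (Hypotheses) and a percentage (Hospital documentation on general information).

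**The concern.** A group-by-time interaction asks whether the difference between groups changes across time points. Hypothesis 1 asks whether the groups differ at the time points after discharge. These are different quantities. If the intervention prevents early readmissions and the gap then holds to 36 weeks, hypothesis 1 is fully satisfied, yet the interaction over the post-discharge points is zero.

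The discharge time point makes this worse. A readmission after discharge cannot have happened by discharge, so the value there is zero for everyone or undefined. Whether that zero enters the model, and whether later values are cumulative or per period, decides what the interaction measures. The article fixes neither.

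Reducing rehospitalization is a central aim, and integration into regular care is planned if efficacy is shown. A verdict on this outcome that turns on an unstated coding is weak support for that decision.

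**Working it through.** **Own figure.** The plan gives no power, alpha or effect size for readmissions, so there is no stated figure to reproduce.

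**Inputs from the article.** 25 children or adolescents per group (Calculation of the sample size); assessments at 8, 24 and 36 weeks (Pre-post-follow-up assessment); reported rehospitalization of 12 to 57% (Background).

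**Assumptions.** Two-sided alpha 0.05; the readmission rates below, whose control-group 36-week values lie inside the 12 to 57% range; a 0/1 indicator of first readmission, with repeat readmissions not modelled; no dropout.

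**Step 1: what the interaction sees.** It is zero when the group differences are equal at all time points entered.

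*Constant difference*, cumulative 35/42/48% against 5/12/18%:
- Cumulative, post-discharge points only: 35−5 = 30, 42−12 = 30, 48−18 = 30. No interaction.
- Cumulative with the discharge zero: 0, 30, 30, 30. Interaction present.
- Per period: 35−5 = 30; (42−35)−(12−5) = 0; (48−42)−(18−12) = 0. Interaction present.

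*Proportional reduction of 60%*, cumulative 30/45/55% against 12/18/22%:
- Cumulative: 18, 27, 33. Per period (30/15/10 against 12/6/4): 18, 9, 6. Interactions present but modest.

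**Step 2: power at 25 per arm.** Monte Carlo of the mixed-ANOVA interaction with Greenhouse-Geisser correction:

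- Constant difference: about 5% (cumulative, no discharge zero), 63 to 68% (per period, without and with the zero), 75% (cumulative with the zero).
- Proportional reduction: from about 11% (per period, no zero) to 64% (cumulative with the zero).

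**Step 3: a second set of rates.** 40% against 15% by 36 weeks, with the timing of events varied; 3000 runs, so the Monte Carlo standard error is at most √(0.25/3000) = 0.9 points. The last column is a two-proportion test at 36 weeks.

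| Timing of events | Cumulative | Cumulative + zero | Per period | Per period + zero | Direct test |
|---|---|---|---|---|---|
| Whole difference by week 8 | 4% | 59% | 54% | 58% | 51% |
| Proportional, front-loaded | 16% | 49% | 12% | 16% | 53% |
| Evenly spread | 31% | 47% | 5% | 7% | 52% |

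The direct test is stable at 51 to 53% (its size at 25 per arm was 6.7%, so this is slightly flattering). The interaction runs from 4% to 59%. At 200 per arm, the cumulative coding in the first row still has 4% power and the per-period coding in the last row 5%. More patients do not help where the test targets a quantity that is zero.

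**Step 4: type I error.** With no effect (40% in both groups), the corrected interaction rejects in 4.7 to 5.6% of runs at 25 per arm.

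**Step 5: satisfaction.** With one time point the interaction has (2−1)×(1−1) = 0 degrees of freedom. An ordinary two-group comparison has 50−2 = 48.

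**The case against.** **The ANOVA sentence may not be meant for readmissions.** The Table 1 row is shared, so the marks at admission and discharge could belong to the general information. The surrounding text refers to scoring by manual and to missing questionnaires, and the success paragraph echoes hypothesis 3. This is a plausible account of intent. But the sentence covers all outcomes measured pre-post-follow-up, the row is so marked, and the success rule has no limit. If the intent was narrower, the remedy is to say so.

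**The interaction can detect a readmission difference.** This stands. With cumulative coding and the discharge zero entered, its power is comparable to a direct test. A reader might infer from the 5% figure that the plan cannot test hypothesis 1, or that 5% is the plan's power. The documents support neither, because 5% belongs to one of several codings that the text leaves open.

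**Inflated type I error.** A reader might also infer this from the structural zero, since an uncorrected analysis gave 7.8% in one simulation. The article does not rule out a sphericity correction, and with one the error is about 5%.

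**Satisfaction.** A reader might infer that hypothesis 2 has been given an impossible test. It has not. Satisfaction is measured only at post, so the ANOVA sentence excludes it by its own terms. Hypothesis 2 already fixes contrast, direction and time point, and the unnamed two-group test is detail an article may leave to an analysis plan.

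**Conclusion.** The concern holds for readmissions. The stated success criterion fits hypotheses 3 and 4 and does not fit hypothesis 1, which is a difference in level of a sparse count or proportion. For one true effect at 25 per arm, interaction power ranges from about 5% to 75% (constant 30-point difference) or 11% to 64% (proportional 60% reduction), according to coding choices the article does not state. The exact figures rest on the assumed rates, timing and alpha. The mismatch itself rests only on the wording of the Hypotheses, Table 1 and Statistical analyses. The right description is mismatched and coding-dependent, not untestable. A mixed ANOVA also yields a group main effect, which is closer to hypothesis 1, but the success rule does not use it.

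**What to change.** - **Interaction rule.** Among the primary outcomes, limit the interaction success rule to quality of life and symptom severity.
- **Readmissions.** Fix one definition, reconciling number, rate and percentage, and compare the groups directly. One option that keeps the stated outcome is the number of readmissions from discharge to 36 weeks by Poisson or negative binomial regression, with cumulative proportions at 8, 24 and 36 weeks alongside. Time to first readmission could support this if the hospital documentation holds the dates. The article does not say that it does, so it should not replace the stated outcome.
- **Satisfaction.** For consistency, add that it is tested by a two-group comparison at 8 weeks.

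The cost is a change of analysis wording. Hospital documentation is already the planned source, and no visits, instruments or patients are added. The change should be made and dated before anyone sees outcomes by group; the article reports the trial as still recruiting.

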The innovative aftercare program DigiPuR (“Digital gestützte Psychotherapie und Reintegration”, digitally supported psychotherapy and reintegration) aims to stabilize and ideally expand treatment successes after partial or full inpatient child and adolescent psychiatric treatment, therefore reducing a worsening of symptoms and rehospitalizations. In the intervention group, direct communication via secure and regular video calls and a messenger system between the hospital, family, and school, as well as, if needed, external support systems, are established. Thereby, problems can be identified and addressed early from multiple perspectives and transitions into outpatient structures can be arranged where necessary. Taking the social environment of children and adolescents into consideration when examining emotional and behavioral problems is consistent with the principle of multisystemic therapy [44]. Efficacy of this digital aftercare in the intervention group is compared to an active control group with regular aftercare within a randomized controlled trial using a naturalistic parallel group study design. A longitudinal pre-post-follow-up assessment at admission, discharge, and 8, 24, and 36 weeks after discharge supplemented by a daily smartphone-based ambulatory assessment from a triadic perspective of patients, parents, and teachers allows for a close investigation of between-person differences and within-person processes in patients’ daily lives. The supplemented ambulatory assessment moreover allows ecologically valid measurements in participants’ daily lives, at the same time reducing retrospective bias [45]. Answers from the ambulatory assessment are graphically processed for the therapists on a weekly basis during aftercare [37]. The assessments are based on the comprehensive conceptual model of outcomes of mental health care for children and adolescents [46]. Accordingly, treatment success and service effectiveness are not only considered as symptom reduction on the individual level, but also related to interactions with the environment in different settings (e.g., home, school, community) [46]. The model proposes five outcome domains (symptoms, functioning, consumer perspectives, environments, systems) in which impact of interventions can be seen [46]. To address these domains, the assessments in DigiPuR include a multi-perspective view on the reintegration phase and instruments used for assessment reflect the domains. The comprehensive assessment serves to examine the general applicability and acceptance as well as the efficacy of this new digital aftercare program for the development of structures specifically for aftercare. Implementing DigiPuR in clinical practice thereby requires a balancing of scientific comparability and practical feasibility in the conception of the design as well as in the scientific evaluation, focusing on aftercare which is flexible and tailored to the needs of the individual patients.

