#### Pre-post-follow-up assessment

Admission and discharge assessment as part of the standard hospital assessment are carried out on paper questionnaires (in exceptions where necessary online) through trained staff during the partial or full inpatient hospital stay in the period from preliminary talk to admission until 1 week after admission and in the period from 1 week before discharge until discharge (pre). For the post, follow-up 1, and follow-up 2 assessment (8, 24, and 36 weeks after discharge), the participants receive an e-mail containing a link for an online survey on the SoSci Survey platform [50], which they can respond to at home via the browser of their computer, tablet, or smartphone within 1 week. At each time point of assessment, the survey lasts no longer than about 45 min.

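### Quality of life and symptom severity are decided by an omnibus group-by-time interaction with pre-treatment scores as outcome levels; one prespecified baseline-adjusted contrast would state a direction and, if the effect lasts, give clearly more power

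*Protocol article*

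**What the plan says.** The Statistical analyses section assigns the model: "All outcome variables measured pre-post-follow-up will be analyzed with separate mixed ANOVAs". It lists the terms: "Predictors will be group (intervention vs. control) and time point, as well as their interaction". It then sets the criterion: "Treatment success would be demonstrated by a significant interaction effect of group and time point", with the further condition of "being shown, through adequate post hoc test, to be due to different time-effects in the two groups".

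The waves come from the Background: "A longitudinal pre-post-follow-up assessment at admission, discharge, and 8, 24, and 36 weeks after discharge". The section Pre-post-follow-up assessment labels the discharge measurement as pre. Table 1 marks symptom severity and quality of life at admission as well. Nothing settles whether admission is a level of the time factor, so that factor has 4 or 5 levels.

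The hypotheses are directional. For quality of life: "Third, we hypothesize health-related quality of life to develop better over time (pre-post follow-up) in the intervention group than in the control group". Hypothesis 4 has the same form for symptom severity. The analysis section repeats the expectation: "Rather, we expect the intervention group to develop better over time than the control group".

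**The concern.** The scientific question is whether the intervention arm does better after discharge. The decisive test is broader. With 3 or 4 degrees of freedom it responds to any departure from parallel profiles, including differences among weeks 8, 24 and 36. If admission is a level, it also responds to the change from admission to discharge, which precedes aftercare. Because pre-treatment values enter as outcomes, their prognostic information is not used as regression adjustment would use it.

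The F statistic is the same for benefit and for harm of equal size. The post hoc condition asks only that the time effects differ between arms. For the ambulatory data the same section does require that the interaction arise from the intervention arm developing better; that condition is not written for these two primary outcomes.

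At stake are the power of a trial with 25 children per arm and a success rule that, as written, names neither a decisive time point nor a required sign.

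**Working it through.** **No figure to reproduce.** Calculation of the sample size gives 25 per arm without effect size, SD, alpha or power.

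**Inputs.** From the document: n = 25 per arm; three post-discharge waves; one or two pre-treatment waves. Assumed: SD 1 at each wave, equal correlation ρ = 0.5 between waves, two-sided 0.05, complete data, arm difference 0 before discharge and 0.6 SD at week 8. The only guide to ρ is the KIDSCREEN-27 retest coefficient of .61 to .74.

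**Omnibus interaction.** With δ_t the arm difference at wave t and T levels, λ = (n/2) × Σ(δ_t − mean δ)² / (1 − ρ), referred to F with T − 1 and (T − 1)(2n − 2) df.
- 4 levels, sustained effect: mean δ = 0.45; sum of squares 0.45² + 3 × 0.15² = 0.27; λ = 12.5 × 0.27 / 0.5 = 6.75; F(3, 144); power 56%.
- 5 levels: mean δ = 0.36; sum of squares 2 × 0.36² + 3 × 0.24² = 0.432; λ = 10.8; F(4, 192); power 74%.
- Reversing the sign of every δ leaves λ unchanged, so harm of the same size is declared significant equally often.

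**Averaged contrast, 1 df.** The mean of three waves has variance (1 + 2ρ)/3 = 0.667. Adjusting for a pre-treatment value with correlation r leaves 0.667 − r², and SE = √(2/n × residual variance).
- r = 0.5: residual 0.417; SE = √(0.08 × 0.417) = 0.183; 0.6/0.183 = 3.29; t with 47 df; power 90%.
- Admission only, r = 0.3: residual 0.577; SE = 0.215; 0.6/0.215 = 2.79; power 78%.

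**Week-8 contrast, r = 0.5.** Residual 1 − 0.25 = 0.75; SE = 0.245; 0.6/0.245 = 2.45; power 67%. With r = 0.3: SE = 0.270; power 59%.

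Power (%) by effect pattern, same formulas:

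| Effect at weeks 8/24/36 | Omnibus, 4 levels | Omnibus, 5 levels | Averaged contrast, r = 0.5 | Averaged contrast, admission only, r = 0.3 | Week-8 contrast, r = 0.5 |
|---|---|---|---|---|---|
| 0.6/0.6/0.6 | 56 | 74 | 90 | 78 | 67 |
| 0.6/0.4/0.2 | 43 | 52 | 57 | 45 | 67 |
| 0.6/0.3/0 | 52 | 54 | 36 | 28 | 67 |

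Simulation agrees to within about two points. It gives 55%, 75%, 89% and 78% in the first row, 57-58% for the contrast against 45-54% in the second, and 35% against 53-55% in the third. Null rejection is about 5% for all tests.

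If admission correlates only 0.3 with the post-discharge waves, the 5-level omnibus falls too. Simulated, it has 65-66% for the sustained effect and 44-45% for the slow fade. The admission-adjusted contrast then still leads for a sustained effect (78%) and ties for a slow fade (45%).

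**Other inputs, sustained effect.** For ρ from 0.4 to 0.6 at 0.6 SD: omnibus 48-67% (4 levels) and 65-84% (5 levels), contrast 88-93%. At 0.5 SD and ρ = 0.5: 41% and 56% against 77%; 80% power needs 59 or 41 per arm for the omnibus and 28 for the contrast. At 0.5 SD, ρ = 0.7 and 5 levels the gap narrows to 81% against 88%.

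**Which pre-treatment value is available.** Randomization and blinding says participants learn their group at the technical briefing. Ambulatory assessment ties that briefing to the start of the daily survey, 2 weeks before discharge. Pre-post-follow-up assessment places the discharge questionnaire in the last week before discharge. By this schedule the discharge score normally follows disclosure of allocation, so admission is the safe covariate.

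**The case against.** The interaction test is valid, holds its 5% error rate and matches a hypothesis about courses over time. That stands: this is a matter of efficiency and of fixing the decision rule, not of bias.

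Four stronger readings are tempting, and the documents do not support them.

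- **That power is lost in every case.** The video calls stop 8 weeks after discharge, so fading is plausible. If the effect is gone by week 36, the averaged contrast is the weaker test. Nor does admission as a fifth level simply waste degrees of freedom: under equal correlation and a sustained effect it raises omnibus power from 56% to 74%.
- **That the success criterion as a whole has no direction, or that the post hoc test will be picked after the result is seen.** The text and hypotheses 3 and 4 state the expected direction and a post hoc step exists. No sentence says the test will be chosen from the data, and a condensed article may leave its name to the analysis plan. What remains is that the condition actually written asks for a difference, not a benefit.
- **That adjusting for both pre-treatment scores brings power to about 94%.** This needs a discharge score collected before disclosure, which the schedule does not normally provide.
- **That age and unit must be in the model.** They may well be prognostic, but nothing in the article shows it.

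**Conclusion.** The point holds as a recommendation on analysis choice. The article itself fixes an omnibus test with 3 or 4 degrees of freedom as the success rule for two primary outcomes, leaves the number of levels open, and does not write benefit into the condition.

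For an effect sustained to week 36, a single baseline-adjusted contrast raises power from about 55% (4 levels) or 75% (5 levels) to about 89%, or to 78% with a weakly correlated admission score. For a slowly fading effect the gain is small and can disappear; for a vanishing effect the averaged contrast loses. Correlation, effect size and pattern are assumptions, since the protocol gives none of them. All omnibus figures are for the F test alone; the added post hoc step can only lower the chance of declaring success.

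**What to change.** For each of the two outcomes, prespecify one baseline-adjusted group contrast as the success test: the average of weeks 8, 24 and 36, or week 8 if the effect is expected to fade once the calls end. Choose before the data are seen. Require the estimate to favour the intervention and report it with a 95% CI. Use the admission value as covariate, and add the discharge value only where it was collected before allocation was disclosed. Report the time-specific differences and the omnibus interaction as supportive, and state whether admission is a level in that ANOVA. Adjustment for age and unit is optional.

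Cost: no new data, since Table 1 already schedules both instruments at admission. The change does replace the decisive model for these outcomes, so it is more than a rewording. The averaged contrast is weaker if the effect exists at one time point only; the week-8 contrast gives up power if the effect lasts (67% against 90% in the table) and has little if the effect grows later.
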